**ii. Sampling procedure**

Eligible children will be randomised to receive either Gelofusin or 4.5% human albumin solution. Most children will receive 20-40mls over the first hour, dependant upon degree of acidosis and physiological improvements in shock. Otherwise, the management the children receive will be identical to our current standard of care. Two groups will be considered:

**Group A: Moderate acidosis**

Children will receive 20mls/kg of either Gelofusin or 4.5% human albumin solution. This will be given over the 30minutes following admission. However, the final volumes given will depend upon the attainment of pre-defined resuscitation targets (see later). Each intervention arm should contain at least 10 children in coma (Blantyre coma score ≤2).

**Group B: Severe acidosis**

Children will receive 40mls/kg of either Gelofusin or 4.5% human albumin solution. This will be given over the first hour following admission. However, the final volumes given will depend upon the attainment of pre-defined resuscitation targets (see later). Each intervention arm should contain at least 10 children in coma (Blantyre coma score ≤2).

The anticipated volumes are based upon the results of the previous pilot data9 and are identical to those given during the randomised trial14. However, in this study the final volume of fluids given to both study groups and for both intervention will ultimately depend upon the satisfactory attainment of resuscitation goals. The initial management and resuscitation targets are covered under the follow section.

# **Definition and treatment goals for children with hypovolaemic shock**

These have been adapted from the international consensus statement for paediatric shock5.

**Level one:** **Assessment for decreased perfusion and alteration of mental status (agitation, prostration or coma):** capillary refill > 2 seconds (cold shock) or flash capillary refill (warm shock), diminished (cold shock) or bounding (warm shock) peripheral pulses, mottled cool extremities (cold shock), or decreased urine output of 1 mL/kg/hr.

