**b) Study Population**

Children > 3 months old with severe falciparum malaria will be considered.

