## Inclusion criteria

Presence of a severity feature (impaired consciousness and/or deep breathing) plus the presence of metabolic acidosis (base excess <-8).

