**Level one goals (all of the following)**

Heat rate within threshold range for age

Systolic blood pressure (BP) within threshold range for age

Capillary refill time <3secs

Oxygen saturations > 95% in room air

Table of the threshold heart rates, mean blood pressure and perfusion pressure (MAP-CVP) for age

| **Age (years)** | **Heart rate *(beats/min)** | **Systolic BP**  **(cm Hg)** | **Perfusion pressure (MAP-CVP)** |
| --- | --- | --- | --- |
| **Newborn** | 120–180 | 70 | 55 |
| **-1** | 120-180 | 75 | 60 |
| **-2** | 120-160 | 80 | 65 |
| **-7** | 100-140 | 85 | 65 |
| **-15** | 90-120 | 85 | 65 |

*should be only be assessed after the termination of a seizure

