**Randomisation procedure**

Randomisation will be conducted using a sealed card system. In the case of an emergency, where a child meets the clinical criteria for severe malaria but has evidence of profound shock (systolic blood pressure that is unrecordable or less < 80mm Hg) and volume resuscitation is required immediately, a children will be randomised before the receipt of the laboratory results and whilst consent is being obtained. The first 20mls/kg bolus will be given while the mother or guardian of the child is being consented and blood tests obtained.At this point if consent for the trial is refused or the malaria slide is negative for *P. falciparum* malaria parasites the child’s subsequent management will be as per local clinical protocol and by the attending clinicians’ judgement. The child will be dropped from the analysis of the study and the study number reallocated.

All children will be intensively monitored. The purpose of the intensive monitoring will be to establish the relative dose response and safety of each fluid regime required for correction of volume deficits and to monitor haemodynamic changes (in respiratory rate, oxygen saturation, heart rate, blood pressure and urine output) and clinical response induced by either colloid. To guide further management a central venous pressure line (CVP line) will be inserted into any child that develops refractory shock (failure to attain level one goals after one hour) or features suggestive of pulmonary oedema (development of bilateral fine, basal crepitations and falling oxygen saturations).

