**b) Provisions for data verification and validation.**

Currently all data is directly entered in File-Maker Pro where most variables entered have dichotomous values only and the values for numerical fields are selected from a list. Initial and final diagnoses are also chosen from a list of common diagnoses. The programmes have been written to include logical and range checks and flags for the reduction of duplication errors. Appropriate information quality control procedures are already established. Children fulfilling the admission criteria for the study will be flagged by the computer to alert the admitting physician.

Descriptive statistics will be used to compare the clinical characteristics of the groups at baseline (admission), 30minutes, 1 hr, 4 hrs, 8 hrs, 12 hrs and at 24 hours, by intervention. The major outcomes of interest will be the resolution of clinical features of shock and major side effects or complications; development of abnormal clotting indices, pulmonary oedema and death (as dependant variables) between the different interventions (independent variables). The primary measure of this outcome will compare the proportions attaining level one goals for resuscitation in those receiving albumin and Gelofusin. Using ANOVA baseline (admission) haemodynamic parameters (heart rate, respiratory rate, oxygen saturation, mean blood pressure and coma score) will compared to those at 1 hr, 2 hours and 8 hours between the different intervention groups. For the purpose of analysis percentage mean change in the parameter will be used between the baseline and next time point.

Expected outcome: We have shown that albumin results in low mortality (< 5%), whilst saline was associated with an overall mortality ~20%, rising to 46% in those with coma. Historical control data from children with the same clinical criteria show mortality was between 30-50%, when volume expansion was not routine. If the dose response to Gelofusin is similar to albumin then assessment of the clinical safety of Gelofusin will take the above mortality data into consideration, as well as the evidence arising from the coagulation studies.

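### The primary measure is read as correction of shock, but shock is not required at entry, children already at goal before fluid are counted as successes, and the level one goals conflict with the protocol's own shock signs

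*Protocol*

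**What the plan says.** - **Entry.** Section 8 b): "Children > 3 months old with severe falciparum malaria will be considered". The inclusion criterion is "Presence of a severity feature (impaired consciousness and/or deep breathing) plus the presence of metabolic acidosis (base excess <-8"). No sign of shock is required, and the exclusion criteria do not remove children without shock. Both acidosis groups are assigned colloid.
- **Shock signs.** Under the definition and treatment goals, level one opens with "Assessment for decreased perfusion and alteration of mental status (agitation, prostration or coma"). It then lists "capillary refill > 2 seconds (cold shock) or flash capillary refill (warm shock), diminished (cold shock) or bounding (warm shock) peripheral pulses", followed by "mottled cool extremities (cold shock), or decreased urine output of 1 mL/kg/hr".
- **Level one goals.** All four must be met: heart rate within the age range, systolic pressure at the age threshold, "Capillary refill time <3secs", and oxygen saturation above 95% in room air. Urine output enters only at level two.
- **Systolic thresholds.** The goals table gives 75 in the row labelled -1 and 80 in the row labelled -2. The randomisation procedure describes profound shock, without regard to age, as "systolic blood pressure that is unrecordable or less < 80mm Hg".
- **Outcome.** Section 8 d) i) makes correction of shock, and the colloid volume needed for it, the primary endpoints. Section 9 b) names resolution of the clinical features of shock as a major outcome and then says "The primary measure of this outcome will compare the proportions attaining level one goals for resuscitation" between albumin and Gelofusin.

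**The concern.** A proportion corrected is meaningful only for children who had something to correct. Here the denominator is every randomised child, and baseline goal status plays no part. A child at goal on arrival who stays there is scored a success whichever fluid was given. Such children add equally, in expectation, to both arms and pull the two proportions together. Section 9 b) treats a response similar to albumin's as the condition for going on to weigh Gelofusin's safety, so the pull is towards the result that favours Gelofusin.

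The volume endpoint is affected in the same way. A child at goal before fluid still receives the first 20 ml/kg, passes the 30-minute assessment, and can be recorded as having needed 20 ml/kg for correction.

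Separately, the signs that define shock and the goals that mark its correction contradict each other on capillary refill, and two sections classify the same infant blood pressure differently. A child can then be in shock by one section and satisfy the matching goal in another.

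**Working it through.** **1. Shock signs against level one goals**

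| Feature | Shock sign? | Level one goal? | Conflict |
| --- | --- | --- | --- |
| Refill between 2 and 3 s | Yes (above 2 s) | Meets it (below 3 s) | Yes |
| Flash refill | Yes (warm shock) | Meets it (no lower limit) | Yes |
| Pulses, extremities | Yes | Not a goal | Not assessed |
| Mental status | Yes | Not a goal | Not assessed |
| Urine output | Yes | Level two only | Not at level one |
| Heart rate, systolic pressure, saturation | No | Yes | Not in the definition |

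Capillary refill is the only feature in both lists. The 2-3 s overlap matters only if refill is recorded more finely than in whole seconds, which the Protocol does not state. The flash-refill conflict does not depend on that.

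**2. Systolic pressure**

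I read the row labelled -1 as up to one year, the single table value as a minimum, and the unit as mmHg. An eligible infant with systolic 75-79 is then below 80 (profound shock in the randomisation procedure) and at or above 75 (at the pressure goal). From the -2 row upwards the thresholds are 80 or 85, and no such conflict arises.

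**3. How many children could be at goal before fluid**

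The Protocol gives no share. The nearest evidence is the pilot in Section 4, which had almost the same entry rule. It reports refill of 3 s or more among the admission features of all 53 children, so 0 of 53 met the refill goal and none could meet all four goals.

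- Exact 95% upper limit for 0/53: 1 - 0.025^(1/53) = 0.067, or 6.7%.
- Chance of 0/53 if the true share were 10%: 0.9^53 = 0.004.
- Chance if it were 30%: 0.7^53 = about 6 in a billion.

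**4. Effect on the comparison**

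Let b be the share at goal before fluid, equal in both arms, with these children staying at goal. Observed attainment is b + (1 - b) × p, so a true difference D shows as (1 - b) × D. For illustration only, take p = 60% and 80% among children off goal (D = 20 points). Power is by normal approximation, two-sided 0.05, with 40 per arm from the 2 × 2 × 20 layout in Section 8 c).

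| b | Observed rates | Difference | Power, all children | Power, off-goal children only |
| --- | --- | --- | --- | --- |
| 0 | 60.0% v 80.0% | 20.0 | 0.50 | 0.50 |
| 6.7% | 62.7% v 81.3% | 18.7 | 0.46 | 0.47 |
| 10% | 64.0% v 82.0% | 18.0 | 0.44 | 0.46 |
| 30% | 72.0% v 86.0% | 14.0 | 0.33 | 0.37 |

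The last two rows lie above the pilot's upper limit and only show how the effect grows. At 6.7% of 80, about 5 children would be affected.

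**The case against.** **The pilot implies that almost no child will be at goal.** This stands and limits the size of the point. A reader might infer from the entry rule that 10-30% of children would be scored as corrected without treatment effect. The pilot speaks against that. The case-note review in Section 4, which found shock in 84% of deaths, does not rescue it: it covers deaths only and scores shock as hypotension or two or more other features. It does not give the share meeting all four goals.

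**Recognition signs and treatment targets need not be the same list.** Also fair. That pulses or mental status are absent from the goals is not in itself an error, and urine output is picked up at level two. What remains is direct contradiction on the one shared feature, refill.

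**Warm shock may be rare here.** The section concerns hypovolaemic shock and the pilot reports prolonged refill. A child with flash refill attains level one only if heart rate, pressure and saturation also pass. The Protocol gives no frequency, so it does not support the stronger reading that warm-shock children will commonly be scored as resolved.

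**Restricting the set gains little power.** True, as the table shows. The gain is in meaning: the measure then describes correction.

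**Analysis sets are usually left to the SAP.** Often so. But the Protocol itself fixes this measure and calls it resolution of shock, and the contradictions are between its own sections.

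**The systolic figures serve different purposes.** One triggers emergency randomisation and the other is a target, and the row label may be damaged in the text available. The overlap is narrow, but if the table reads as shown the two still need reconciling.

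**Conclusion.** The point holds, with modest effect. The Protocol does not require shock at entry, does not tie the primary measure to pre-fluid goal status, and contradicts itself on capillary refill and, for infants, on systolic pressure.

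If the pilot carries over, the share at goal before fluid is probably below about 7%. An illustrative 20-point difference would then shrink by at most about 1.3 points, to 18.7. This rests on the pilot's refill statement applying to every child, on a similar case mix in this trial, and on at-goal children staying at goal. The 60% and 80% rates are assumptions.

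A reader might conclude that every listed shock sign must clear before a child counts as resolved. The documents do not support that as a workable outcome. Coma is one of the signs, impaired consciousness is an entry feature, and at least half the children are to be in coma, so the measure would follow neurological recovery instead of perfusion. Hourly urine output cannot be known at admission.

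**What to change.** 1. Base the primary comparison of level one attainment, and of volume to correction, on children who fail at least one level one goal at the admission assessment before any fluid. Report children already at goal separately, by arm. Keep all children in the safety analyses. The grouping uses pre-fluid status only, so the comparison remains a randomised one.
2. Reconcile the shock signs and the level one goals on capillary refill, including flash refill and the 2-3 s interval, and reconcile the goals table and the randomisation procedure on systolic pressure in infants. This review does not say which threshold is right.
3. Do not add mental status or urine output to the resolution outcome.

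The cost is a sentence of outcome wording and one baseline flag built from the four level one parameters, which must be recorded before the first bolus, including in emergency cases. The primary set becomes slightly smaller than 80, by about 5 children at the pilot's upper limit.

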**Maintain airway, give oxygen and a**

**rapid infusion of 20mls/kg of colloid.**

Assessment at 30 minutes for level 1 goals of successful resuscitation

**Level 2: level one goals not achieved**

**Maintain airway and give oxygen.**

**Administer a further bolus of 20mls/kg of colloid**.

Assessment at 1 hour for level 1 goals of successful resuscitation.

(note: For children receiving > 20mls/kg of colloid we plan to insert a CVP line for the purposes of safety. The fixing of central line will not delay the administration of the second 20mls/kg of resuscitation, since this may be deleterious to the child.)

# **Level three: failure to achieve level one goals after 40mls/kg of colloid**

Assessment of CVP and perfusion pressure. For those with a CVP ≤8cm water or a perfusion pressure < threshold targets further bolus of colloid will be given ( in 10mls/kg aliquots) until CVP >8cm water or perfusion pressure threshold achieved and urine output > 1ml/kg/hr (level two goal).

**Level four: fluid refractory shock:** Failure to achieve level two goals after 80mls/kg, consider dopamine.

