## Level two goals

CVP > 8 cm H20 or attainment of threshold perfusion pressure (see table)

plus urine output> 1mls/kg/hour.

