**Potential complications**

The judicious use of intravenous fluids in children with a potential of raised intracranial pressure, cardiogenic shock or fluid overload is a concern. The study will be conducted with continual monitoring of vital and neurological signs. Further boluses of fluid will be withheld if vital and neurological signs indicate raised intracranial pressure (ICP) or heart failure. Raised ICP will be indicated by a rising blood pressure (>90% centile/age), together with a falling heart rate, the development of a sluggish reaction to or asymmetric pupillary reaction to light. Cardiac failure will be indicated by a worsening tachycardia and tachypnoea, de novo presence of fine crepitations in lung bases, deteriorating oxygen saturation and a sustained rise in CVP >15cm. These children will not receive any more fluid boluses and chest x-ray will be performed. Frusemide at 1mg/kg will be given to children in whom pulmonary oedema or right-sided heart failure is suspected or confirmed. In those with suspected raised ICP treatment with mannitol will be considered. The complications of a central venous pressure line include infection, blood loss and thrombosis. These will be minimised by using short CVP lines inserted into the femoral vein and advanced only 6-8 cm. They will remain in-situ for only up 48 hours then removed. The nurse in charge of the patient will only look after a maximum of two patients at one time.

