**11. ETHICAL CONSIDERATIONS.**

i) Do no harm. These children will be closely monitored and fluid boluses given cautiously. Further fluid boluses would be withheld from children showing signs of cardiogenic shock or fluid overload.

ii) Blood samples would be required from all study children. However, the volumes of blood required would be minimized wherever possible and be kept well within the maximum locally agreed volumes (10 mls per patient over the period of the study).

iii) Informed consent will be sought from all families involved in the proposed studies (see attached consent form).

iv) Information pertaining to children involved in the proposed studies would be kept on secure password protected databases. In addition, personal data would be indexed using unique identification numbers rather than personal names.

v) The well being of the sick child is paramount. Therefore, at any time the supervising physician can override the requirements of the study if there were a clinical deterioration.

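### The level three start rule for boluses conflicts with its own stop rule, the level two goal, in 2 of 8 clinical states, and leaves 1 further state without an order

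*Protocol*

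**What the plan says.** All of this is in the protocol, section 8.

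- **Start rule (Level three).** It applies to children who have not reached level one goals after 40 ml/kg: "For those with a CVP ≤8cm water or a perfusion pressure < threshold targets further bolus of colloid will be given", in aliquots of 10 ml/kg. Urine output plays no part.
- **Stop rule (same sentence).** Boluses continue "until CVP >8cm water or perfusion pressure threshold achieved and urine output > 1ml/kg/hr (level two goal".
- **Level two goals, defined separately.** First part: "CVP > 8 cm H20 or attainment of threshold perfusion pressure (see table". Second part: "plus urine output> 1mls/kg/hour". This fixes the grouping: either CVP or perfusion pressure is enough, and urine output is always required.
- **Level four.** "Failure to achieve level two goals after 80mls/kg, consider dopamine".
- **Withholding.** Potential complications stops boluses for signs of raised intracranial pressure or cardiac failure. The CVP element of cardiac failure comes in "deteriorating oxygen saturation and a sustained rise in CVP >15cm".
- **Override.** Section 11(v): "at any time the supervising physician can override the requirements of the study if there were a clinical deterioration".

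Clinical procedures (section 8.d.i) names correction of shock and the colloid volumes needed for it as the primary endpoints. Secondary aim 2 compares the volumes needed with the two colloids. Section 9(b) takes the proportion attaining level one goals as the primary measure.

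**The concern.** A rule that starts treatment and a rule that ends it at a named goal should not both be true for the same child at the same moment. Here the start rule joins two deficits with 'or', and the goal joins the two matching successes with 'or' as well. The opposite of 'CVP adequate or pressure adequate' is 'both inadequate', so the rules overlap. Because urine output is in the goal but not in the start rule, they also leave a hole.

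Two things are at stake. One is fluid safety in the sickest children, in a protocol that itself names fluid overload and raised intracranial pressure as concerns. The other is the meaning of the recorded ml/kg. Where the order depends on which half of the sentence the clinician follows, the volume partly measures that choice and not the child's need.

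**Working it through.** **Inputs.** Let C = CVP above 8 cm water, P = perfusion pressure at threshold, U = urine output above 1 ml/kg/h.

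- Start = not C, or not P (Level three).
- Goal met = (C or P) and U (Level two goals).

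**Enumeration of the 2 × 2 × 2 = 8 states.**

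| C | P | U | Start rule | Level two goal | Result |
|---|---|---|---|---|---|
| yes | yes | yes | no bolus | met | consistent |
| yes | yes | no | no bolus | not met | **gap** |
| yes | no | yes | bolus | met | **conflict** |
| yes | no | no | bolus | not met | consistent |
| no | yes | yes | bolus | met | **conflict** |
| no | yes | no | bolus | not met | consistent |
| no | no | yes | bolus | not met | consistent |
| no | no | no | bolus | not met | consistent |

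Result: 2 conflicts, 1 gap, 5 consistent (2 + 1 + 5 = 8). None of C, P and U is itself a level one goal (those are heart rate, systolic pressure, capillary refill and saturation), so failing level one does not by definition exclude any row.

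**Examples**, with a perfusion pressure threshold of 65 (the value in the three oldest age rows of the threshold table):

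- CVP 10, pressure 60, urine 1.5 ml/kg/h: conflict.
- CVP 6, pressure 70, urine 1.5 ml/kg/h: conflict.
- CVP 10, pressure 70, urine 0.5 ml/kg/h: gap.

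**Other grouping.** If the Level three sentence is read alone as C or (P and U), 3 states meet both rules and 0 meet neither. The conflict remains.

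**Sequential reading.** Suppose the start rule governs only entry, and the stop rule governs each reassessment (give unless the goal is met). The same 3 states then receive opposite orders at the two moments. In the two conflict states, entry says give and reassessment says stop. In the gap state, entry says no bolus and reassessment says give.

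**Volume.**

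- Conflict states: one aliquot at entry, 40 + 10 = 50 ml/kg against 40 ml/kg.
- Gap state: 0 ml/kg under the start rule, against up to 80 − 40 = 40 ml/kg (4 aliquots of 10) if boluses run until the goal is met. Level four is framed as failure after 80 ml/kg, so a child given no bolus at 40 ml/kg does not arrive there.

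**Do other sections settle it?** The CVP element for cardiac failure is a sustained rise above 15 cm, so a CVP above 8 and up to 15 without other signs is not covered. The override in section 11(v) needs a clinical deterioration.

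**The case against.** The strongest reply is that start and stop rules need not be complements. The sentence is sequential, and under that reading the conflict costs one 10 ml/kg aliquot at entry. That size is right. It does not remove the problem that identical measurements are ordered differently at entry and at reassessment.

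A second reply reads the two 'or' phrases respectively: low CVP is treated until CVP is corrected, low pressure until pressure is corrected. Both conflict states would then disappear. However, Level two goals defines the goal on its own with either measure sufficing, and Level three labels its stop rule as that goal. The urine output gap would also remain.

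Third, every child here has failed level one goals and, in the conflict states, has a low CVP or a low pressure, so one more small bolus is not evidently wrong clinically. Equally, withholding fluid from a child with adequate CVP and pressure but low urine output is defensible. Both points stand: the fault is in what the protocol orders, not in either clinical choice.

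Fourth, the effect is limited. Sampling procedure expects most children to receive 20–40 ml (per kg, judging by the group A and B doses) in the first hour. A trial team member attends during resuscitation fluids, and the rule is the same in both arms. All of this stands and limits the consequence.

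A reader might infer that the protocol contradicts itself in three states. It does so in two; the third is an omission. A reader might also infer that 3 of 8 states means about 3 in 8 children. The count says nothing about frequency, and CVP and perfusion pressure are linked because pressure is MAP minus CVP. The pilot mean CVP of 7.5 cm (SE 0.5) at 8 hours shows only that values near the cut-off occur. It describes the whole pilot group, not children failing after 40 ml/kg.

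**Conclusion.** The point holds as an error in a stated treatment rule. Two of 8 states are ordered a bolus with the level two goal already met, worth one 10 ml/kg aliquot at entry. One of 8 has no order and no stated route to level four. These counts rest on the grouping that Level two goals gives explicitly; the other grouping changes them to 3 and 0 and does not rescue the rule.

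The reach is narrow: children still failing level one goals after 40 ml/kg, whose number the protocol does not give. For them it bears on fluid safety and on colloid volume, named as a primary endpoint in Clinical procedures and compared in secondary aim 2.

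It would be tempting to conclude that the main comparison is compromised or biased between arms. The document does not support that. The primary measure in section 9(b) uses level one goals, which the algorithm assesses at 30 minutes and 1 hour, before level three begins, and nothing suggests that the arms would be handled differently.

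**What to change.** Reword Level three along these lines:

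> For children who have not met the level two goal and have CVP ≤8 cm water or perfusion pressure below threshold, give a 10 ml/kg aliquot and reassess after each, up to 80 ml/kg, until the level two goal is met or a withholding criterion under Potential complications is present. A child with CVP >8 cm water and perfusion pressure at threshold but urine output ≤1 ml/kg/h receives no further bolus by default and is assessed under level four.

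This gives a bolus in 4 states, stops in 3 and sends 1 to level four (4 + 3 + 1 = 8), with no conflict and no gap. The Level four sentence needs a matching clause so that this child can enter before 80 ml/kg.

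Three alternatives are less good or need more:

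- Changing only 'or' to 'and' in the start rule removes the conflicts but leaves 3 states without an order.
- Giving boluses whenever the goal is unmet is consistent (5 give, 3 stop), but it orders up to 40 ml/kg more for a child with adequate CVP and pressure. That is a clinical trade-off and should not be the default.
- If the clinicians want both CVP and pressure to be adequate, change Level two goals and the Level three stop rule together. That removes the conflicts; the low urine output sentence is still needed.

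The cost is a few lines of text with no new data, visits or patients. The small downside is that the clinicians must confirm the order for the three affected states.

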### Secondary aims

1. To establish whether volume correction by Gelofusin can be undertaken safely and is comparable to albumin.
2. To examine whether the volume of Gelofusin required for correction of the physiological parameters of hypovolaemic shock is similar to albumin.
3. To establish whether albumin or Gelofusin lead to derangements of coagulation.

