**i) Type of data to be collected and collection procedures to be followed.**

## Clinical procedures

The study will be conducted with continual monitoring of vital and neurological signs. Clinical assessment by members of the trial team will occur at 30 mins, 1 hour and followed by hourly (by the nursing personnel) until 8 hours post admission, and thereafter 4 hourly. One of the trial team will be attending to the child when they are receiving resuscitation fluids. Children will be managed according to the attainment of resuscitation goals described previously. The primary endpoints will be the correction of shock and volumes of colloid required to achieve this (ie: level one, level two etc).

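### The level three start rule for colloid overlaps with its own stopping goal, so some children are due a 10 ml/kg aliquot when the goal is already met

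*Protocol*

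**What the plan says.** Section 8 of the protocol sets out stepwise resuscitation. Level three applies to children who have not reached the level one goals after 40 ml/kg.

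- **Start rule (Level three):** "For those with a CVP ≤8cm water or a perfusion pressure < threshold targets further bolus of colloid will be given", in aliquots of 10 ml/kg.
- **Stop clause (same sentence):** "until CVP >8cm water or perfusion pressure threshold achieved and urine output > 1ml/kg/hr (level two goal").
- **Goal (Level two goals):** "CVP > 8 cm H20 or attainment of threshold perfusion pressure (see table"), with urine output above 1 ml/kg/hr required in addition.
- **Next step (Level four):** if the level two goals are still not reached after 80 ml/kg, dopamine is considered.

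The volume given matters to the analysis. Under Group B the protocol says that "the final volume of fluids given to both study groups and for both intervention will ultimately depend upon the satisfactory attainment of resuscitation goals". Under Clinical procedures it says "The primary endpoints will be the correction of shock and volumes of colloid required to achieve this", by level. The second of the secondary aims is "To examine whether the volume of Gelofusin required for correction of the physiological parameters of hypovolaemic shock is similar to albumin".

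**The concern.** The start rule fires if either CVP or perfusion pressure is low. The goal is met if either one is adequate, provided urine output is adequate. The complement of an 'or' trigger is an 'and' goal, but both are written with 'or'. When the two measures disagree and urine output is adequate, the start rule says give 10 ml/kg and the goal says the child is there already. The protocol does not rank CVP against perfusion pressure.

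Two things are at stake. One is fluid exposure, in children for whom the protocol itself treats overload and raised intracranial pressure as risks. The other is the recorded volume of colloid, which is an endpoint. A later analysis plan cannot repair a bedside dosing rule once the fluid has been given.

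**Working it through.** No figure in the plan needs reproducing; the check is one of logic.

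**Inputs** (protocol section 8, Level three and Level two goals). Let C = CVP above 8 cm water, P = perfusion pressure at threshold, U = urine output above 1 ml/kg/hr.

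- Start = (not C) or (not P)
- Goal, as the Level two goals section has it = (C or P) and U

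| CVP | Perfusion pressure | Urine output | Start rule met | Goal met | Result |
|---|---|---|---|---|---|
| ≤8 | low | low | yes | no | bolus |
| ≤8 | low | adequate | yes | no | bolus |
| ≤8 | at threshold | low | yes | no | bolus |
| ≤8 | at threshold | adequate | yes | yes | **conflict** |
| >8 | low | low | yes | no | bolus |
| >8 | low | adequate | yes | yes | **conflict** |
| >8 | at threshold | low | no | no | neither |
| >8 | at threshold | adequate | no | yes | stop |

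Start is met in 6 states and the goal in 3. Both are met in 2, and neither in 1.

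**Other bracketing.** If urine output in the stop clause is tied only to perfusion pressure, goal = C or (P and U). The goal is then met in 5 states. The overlap rises to 3, because CVP >8 with low perfusion pressure and low urine output joins it, and no state is neither.

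**Can the conflict states occur?** Perfusion pressure is defined as mean arterial pressure (MAP) minus CVP, so at a given MAP a lower CVP raises it and a higher CVP lowers it. Illustration, assuming that the threshold of 65 is in mmHg and that 1.36 cm water = 1 mmHg:

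- MAP 72, CVP 5 cm: 72 − 5/1.36 = 68.3. Perfusion pressure is at threshold while CVP is ≤8.
- MAP 68, CVP 10 cm: 68 − 10/1.36 = 60.6. CVP is >8 while perfusion pressure is low.

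Either child can still fail the level one goals on heart rate, capillary refill or saturation. Urine output is not among those goals.

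**Size per affected child.** The start rule is written for the level three assessment, and the stop clause governs afterwards. A child already at goal at that assessment is therefore in dispute for one aliquot.

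- 10/40 = 25% on top of the 40 ml/kg already given.
- Each arm has 20 + 20 = 40 children, so one affected child moves the arm mean by 10/40 = 0.25 ml/kg.
- Within one acidosis stratum of an arm (20 children), the shift is 10/20 = 0.5 ml/kg.

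**Check of the fix.** Start' = [(not C) or (not P)] and not Goal. A bolus is due in 6 − 2 = 4 states, the goal is met in 3, and both hold in 0. The one 'neither' state is left as it is.

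**The case against.** The strongest reply is that the sentence runs in time order. An instruction to give fluid until a condition holds ordinarily requires none once it does. The stop clause names the level two goal, and level four refers back to it, so the goal is the natural governing test and the discordant child should simply get nothing more. This largely stands, and it limits the dispute to one aliquot. It does not remove the conflict: the start rule still directs a bolus for every child with CVP ≤8 cm, and no text says which clause prevails.

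A second reply pairs the criteria: treat low CVP until CVP is corrected, and low perfusion pressure until that is corrected. Level three would then agree with itself. But the Level two goals section and level four would still count either measure as success, so a child would be given fluid past a goal already met.

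A third reply is that the consequences are small. "Most children will receive 20-40mls over the first hour", so level three should be the exception. A trial team member attends while resuscitation fluid is given, response is monitored after each dose, boluses are withheld for signs of raised intracranial pressure or heart failure, and the supervising physician can override the study on deterioration. These points stand as limits on harm and on variation between staff. None of them tells staff what to do for a stable child whose CVP and perfusion pressure disagree.

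A reader might also infer that the 'neither' state has no instruction. At first assessment it does: the start rule is not met, so no level three bolus is given. Withholding colloid when CVP and perfusion pressure are both adequate is clinically coherent. A child who reaches that state while already receiving aliquots continues, because the stop clause is unmet.

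**Conclusion.** The conflict is in the text and survives either bracketing of urine output. It is a modest fault: one disputed 10 ml/kg aliquot per affected child, in the level three subset only. Four stronger readings are tempting, and the protocol does not support them.

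- **That up to four aliquots are in dispute.** Four would fit, (80 − 40)/10 = 4. But this needs either the start rule to be re-applied after every aliquot, which the protocol does not say, or the paired reading, under which the extra aliquots are simply due on the level three wording.
- **That 2 of 8 is a frequency.** It counts combinations of criteria, not children. The protocol gives neither the size of the level three subset nor how often the measures disagree, so the total effect on mean volume cannot be computed.
- **That the comparison of colloids is biased.** Both arms follow the same rule, and nothing shows that it acts differently between them.
- **That the main efficacy measure is undermined.** Section 9(b) says "The primary measure of this outcome will compare the proportions attaining level one goals for resuscitation in those receiving albumin and Gelofusin". Those goals are first assessed at 30 minutes and 1 hour, before this rule acts. The discordant states do not change a child's level either; what varies is the volume recorded.

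The size rests on the planned 40 children per arm and 20 per acidosis stratum within an arm, and on the stop clause governing once aliquots have begun.

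**What to change.** Reword the level three sentence along these lines: *Further 10 ml/kg aliquots are given to those with CVP ≤8 cm or perfusion pressure below threshold who have not met the level two goal; reassess after each aliquot and stop once the level two goal is met.* Keep it subject to the withholding signs under Potential complications and to the existing step at 80 ml/kg. Refer to the Level two goals section for the definition, so that urine output is required whichever haemodynamic measure is met.

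The cost is one sentence. The downside is that some discordant children receive one aliquot fewer than a literal reading of the start rule would give.

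Two choices belong to the clinical team and should not be settled by the rewording. The first is whether a child first assessed with CVP >8 cm, perfusion pressure at threshold and low urine output should receive colloid; as written that child gets no level three bolus, and the wording above leaves this unchanged. The second is whether CVP and perfusion pressure should both be required for the goal, given the protocol's remark in the Background that sick children often need preloads of about 8–10 cm.
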